## Data and safety monitoring board

Before the start of the trial, all members of this study will have special training on clinical trial operation and quality control. A data and safety monitoring board will also be established to ensure data safety and protect the rights and health of all the participants. This independent advisory group will check the data and monitor the execution of scientific and ethical standards of the RCT once a week. Participants’ information will be saved in the specified file folder and provided only with the permission of the data and safety monitoring board.

## Sample size calculation

Our primary outcome is the time to first defecation. The unpublished experimental data on the effects of AA combined with MA, based on a 2-week prior pilot experiment, were used for the sample size calculation. The time to first defecation is 77.8 ± 15.6 h in the intervention group and 85.1 ± 13.35 h in the control group. We chose the two-sample *t*-test model with a two-tailed test, and the relevant calculating parameters are a significance level of 0.05, a power of 0.80, and an allocation ratio of 1:1. The required number of participants per group is 72. Considering a dropout rate of 10%, the sample size for this trial is 80. Thus, a total of 160 participants will be recruited.

## Statistical analysis

The principle of intention-to-treat (ITT) analysis will be followed in the process of statistical analysis. The last observation carried forward (LOCF) analysis will be applied for missing data in ITT analysis. Supplementary per-protocol analysis will also be carried out. All the statistical analyses will be performed using SPSS Ver. 24.0 with a significance level of 0.05.

First, the different baseline characteristics of the two groups will be described, and data will be presented as mean or median with standard deviation or interquartile range for continuous variables and as frequency distributions for categorical variables. Moreover, the histograms, boxes, and other representations will also be considered for the graphic analysis of corresponding data. A two-sample *t*-test for quantitative data or a chi-squared test for qualitative data will be performed as a homogeneity test, and the covariance analysis will also be performed if an adjustment is needed for a baseline characteristic.

Second, the analyses will focus on whether statistically better treatment outcomes could be achieved in the intervention group. *P*-values less than 0.05 will be considered statistically significant, and tests will be two-sided.

In terms of the changes in the measurement data, the two-sample *t*-test or the Wilcoxon rank-sum test will be used to compare the two groups and to determine differences according to normality. The mean change and the interaction between groups and observed time frames will be analyzed using a two-factor repeated measure analysis. If necessary, a mixed model approach will also be used.

Finally, safety analysis will be performed using the chi-squared test or Fisher's exact test based on the frequency and percentage of all recorded adverse events between the two groups.

The above plan is what we intend to do; however, the final analyses reported may differ from those planned, allowing for *post-hoc* analysis where it is indicated.

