## Outcome measures

### Primary outcome measures

The primary outcomes are the time to first defecation and first flatus, which is regarded as a bowel function indicator. This time is calculated from the end of laparoscopic surgery and will be recorded by nurses with accuracy to the hour.

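### LOCF is prescribed for all missing ITT data but is undefined for the single-time primary outcomes; forced through as last contact, it can cost power and, with unequal losses, inflate type I error

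*Protocol article*

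**What the plan says.** The Statistical analysis section of the protocol article gives one rule for missing values: "The last observation carried forward (LOCF) analysis will be applied for missing data in ITT analysis". It names no outcome to which the rule is confined. For comparing the arms, the section offers a two-sample t-test or, as the alternative, says the "Wilcoxon rank-sum test will be used to compare the two groups and to determine differences according to normality". Neither test accommodates censored times, and censoring is not mentioned.

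Under Primary outcome measures: "The primary outcomes are the time to first defecation and first flatus, which is regarded as a bowel function indicator". On how it is measured: "This time is calculated from the end of laparoscopic surgery and will be recorded by nurses with accuracy to the hour". Each patient therefore supplies one defecation time and one flatus time.

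The Sample size calculation section sizes the trial on defecation alone ("Our primary outcome is the time to first defecation") and gives the planning values: "The time to first defecation is 77.8 ± 15.6 h in the intervention group and 85.1 ± 13.35 h in the control group". It allows for 10% dropout, which takes 72 per group to 80.

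**The concern.** LOCF needs an earlier measurement of the same quantity. A time to a first event has none: until the event occurs there is nothing to carry. The stated rule therefore gives the analyst no value for a patient whose first defecation or flatus was not observed.

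If the analyst follows the rule anyway, the nearest available number is the hour of last contact. A patient who leaves at 36 h without having defecated is then scored as having defecated at 36 h, far ahead of planning means of 77.8 and 85.1 h. In truth that patient's time is right-censored at 36 h. False early times widen the spread in both arms. If one arm loses more patients, that arm also looks faster.

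The protocol expects some loss: it budgets for 10% dropout and withdraws participants after severe adverse events. Unequal loss is plausible because participants are unblinded and only one arm has daily needling, but the article does not predict it.

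For the inflammatory markers, LOCF can be carried out but is a poor choice. It would enter a value from the first postoperative day as the discharge value.

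**Working it through.** **1. The plan's own figure.** Difference 85.1 − 77.8 = 7.3 h; alpha 0.05, "with a two-tailed test"; power 0.80. With the larger SD in both arms, n = 2 × (1.960 + 0.842)² × 15.6² / 7.3² = 2 × 7.85 × 243.36 / 53.29 ≈ 71.7, so 72 per arm, and 72 / 0.90 = 80. This reproduces the article. With both stated SDs, the root-mean-square SD is √((15.6² + 13.35²)/2) = 14.52. On that basis 72 observed patients per arm give power of about 0.85 and 80 give about 0.88. The reference without LOCF is therefore 0.85, not 0.80.

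**2. Where LOCF has something to carry.**

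| Outcome | Measured | Earlier value? |
|---|---|---|
| First defecation, first flatus | once | none |
| VAS pain, distension | day 1, discharge | yes |
| Inflammatory markers | baseline, day 1, discharge | yes |

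**3. Hand check of the last-contact reading.** Assume 10% loss per arm, with last contact uniform on 24–48 h (mean 36, variance 24²/12 = 48).

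- Difference: 0.9 × 7.3 = 6.57 h.
- Intervention variance: 0.9 × 15.6² + 0.1 × 48 + 0.09 × (77.8 − 36)² = 219.0 + 4.8 + 157.3 = 381.1.
- Control variance: 0.9 × 13.35² + 0.1 × 48 + 0.09 × (85.1 − 36)² = 160.4 + 4.8 + 217.0 = 382.2.
- Standard error: √((381.1 + 382.2)/80) = 3.09; ratio 6.57/3.09 = 2.13.
- Power ≈ Φ(2.13 − 1.96) = 0.57, close to the simulated 0.58.

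The SD rises from about 14.5 to 19.5. That increase, more than the smaller difference, is what costs power.

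**4. Power over assumed timings.** Simulation with normal times at the planning values, 80 per arm, 10% loss in each arm. Where two figures are shown, one treats loss as a 10% chance per patient and the other as exactly 8 per arm.

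| Assumed hour of loss | t-test | rank-sum (approx.) |
|---|---|---|
| 0–24 | 0.28–0.38 | 0.70 |
| 24–48 | 0.58 | 0.74 |
| 48–72 | 0.77–0.80 | 0.76 |
| 60–80 | 0.85 | 0.83 |
| LOCF dropped, about 72 observed per arm | 0.85 | 0.85 |

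**5. Type I error.** Common mean 81.45 h (midpoint of the planning means), SD 14.52.

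- Equal 10% random loss: 0.048–0.051 (t-test), 0.049–0.057 (rank-sum). Exactly 8 v 8 at 24–48 h: 0.006 and 0.023, which is conservative.
- Mild imbalance, 5 v 3 at 24–48 h: 0.035 and 0.044.
- Marked imbalance, 15% v 5%: the spurious difference is about (0.15 − 0.05) × (81.45 − mean hour of loss). That is 0.10 × 69.45 = 6.9 h for 0–24 h and 0.10 × 21.45 = 2.1 h for 48–72 h. Over the timings before 72 h, the error rate is about 0.11–0.42 (t-test) and 0.12–0.19 (rank-sum).
- With a true 7.3 h effect and the heavier loss in the control arm (5% v 15%), t-test power falls to 0.05–0.43.

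**6. Alternatives, 8 v 8 losses at 24–48 h.** The observed-case t-test has power of about 0.85. The generalised Wilcoxon test, with these patients censored, has 0.84–0.85 and type I error of about 0.05. The log-rank test has only about 0.61–0.66. It gives relatively more weight to late times, where the planning distributions converge: two SDs below the means the arms are 58.4 − 46.6 = 11.8 h apart, two SDs above only 111.8 − 109.0 = 2.8 h.

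**The case against.** The best defence is that LOCF was meant only for outcomes with a prior value, such as pain and the markers, and that outcome-by-outcome rules sit in a fuller document. That may be so, and a condensed article need not spell everything out. But this is not an omission. The sentence as printed covers the whole ITT analysis, and for the outcome that sized the trial it cannot be executed.

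The defence is right that entering last contact is only one reading. A reader might infer that it is the only possible one, and that the ITT result is therefore bound to be invalid. The article does not say what value would be entered, so neither follows. Patients lost before surgery, which is possible because auricular treatment begins three days earlier, have no postoperative hour to enter at all.

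It is also fair that the damage depends on timing. Losses at 60–80 h leave t-test power essentially intact, so no single figure should be quoted as the cost.

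Finally, most of the simulated gain comes from dropping LOCF, since observed-case analysis recovers it. The choice of the generalised Wilcoxon test is secondary. Its good behaviour here assumes that loss is unrelated to the event time, which withdrawal after a severe adverse event may contradict.

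**Conclusion.** The point stands in a conditional form. What is certain from the text is that the stated missing-data rule does not fit single event times and leaves the primary ITT analysis undefined for patients without an observed event.

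The numerical consequences rest on three things the article does not give: that last contact is entered as the event time, when losses occur, and how they split between arms. They also rest on normal times at the planning values for defecation; no planning values are given for flatus. On those assumptions, 10% loss per arm costs anything from almost nothing to more than half of the power.

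A reader might infer that LOCF inflates the false-positive rate in any case. It does not: with equal losses, or a mild imbalance such as 5 v 3, the rate stays near or below 0.05. Inflation requires a marked imbalance, which is plausible in this unblinded design but not stated.

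A reader might also infer from Table 1, which places both events at the visit on days 1–3, that recording stops at 72 h and most patients would be censored. The outcome section sets no such limit, and none of the figures above relies on one.

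**What to change.** State that LOCF does not apply to time to first defecation or first flatus. Treat a patient without an observed event as censored at last contact, and name one censored-data comparison in advance. The generalised Wilcoxon test is a natural candidate: it is the censored counterpart of the rank-sum test already planned and is a standard procedure. The test should be fixed before the data are seen, because power differs materially between candidates.

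Add a sensitivity analysis for informative loss, covering in particular patients withdrawn after a severe adverse event. For VAS pain and the inflammatory markers, replace LOCF with the mixed model that the Statistical analysis section now holds in reserve.

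The cost is wording and a routine analysis step, plus about 1–2 points of power relative to the t-test if no data are missing (about 0.86 v 0.88 at 80 per arm). The article reports the trial as still recruiting, so the change should be recorded before the data are analysed.

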## Eligibility criteria

### Inclusion criteria

(1)Age ranging from 18 to 80 years;(2)Having upper gastrointestinal disease who will receive elective laparoscopic surgery, including benign hepatobiliary diseases, pancreatic diseases, gastric diseases, and malignant non-metastatic tumors;(3)Willing to sign the informed consent form and participate in the clinical trial.

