#### Inflammatory index

The inflammatory index includes white blood cell (WBC) count and the levels of C-reactive protein (CRP), interleukin-6 (IL-6), procalcitonin (PCT), and tumor necrosis factor-α (TNF-α), which will be obtained at baseline, 1 day after surgery, and at the time of discharge.

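### Covariance analysis is done only if baseline comparisons seem to call for it, with no covariate named and no primary result chosen, which gives up most of the available precision

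*Protocol article*

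**What the plan says.** All of the following is in the protocol article.

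- **Statistical analysis, baseline.** A two-sample t-test or a chi-squared test on baseline characteristics "will be performed as a homogeneity test". The same sentence adds that "the covariance analysis will also be performed if an adjustment is needed for a baseline characteristic". No covariate is listed, no criterion for need is given, and adjusted and unadjusted results are not ranked.
- **Statistical analysis, group comparison.** The default is an unadjusted t-test or Wilcoxon rank-sum test, chosen by normality. A two-factor repeated-measures analysis, with a mixed model if necessary, covers change over time. The section closes by allowing the reported analyses to depart from the plan.
- **Inclusion criteria.** Elective laparoscopic surgery for upper gastrointestinal disease, "including benign hepatobiliary diseases, pancreatic diseases, gastric diseases, and malignant non-metastatic tumors".
- **Randomization and blinding.** Blocks of four; no stratification factor is described.
- **Inflammatory index.** Five markers, "which will be obtained at baseline, 1 day after surgery, and at the time of discharge".
- **Sample size calculation.** A two-sample t-test on time to first defecation, "77.8 ± 15.6 h in the intervention group and 85.1 ± 13.35 h in the control group", with "a significance level of 0.05, a power of 0.80, and an allocation ratio of 1:1"; 72 per group, or 80 with 10% dropout.

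**The concern.** When allocation is random, any baseline difference between groups is due to chance. A significance test of that difference therefore says nothing about whether the variable predicts time to first defecation. A rule that adjusts when such a test is significant will adjust for an irrelevant variable that happens to differ, and will leave out a strong predictor that happens to be balanced. A balanced predictor still carries outcome variance, and removing that variance is the main gain from adjustment.

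The trial has obvious candidates. Organ group (hepatobiliary, pancreatic, gastric) and malignant versus benign disease vary by design, and neither the described randomisation nor the default analysis takes account of them.

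Two things are at stake. One is precision, in a trial sized for 80% power. The other is that covariance analysis is done in addition to the unadjusted test with no ranking, so two results may exist and the choice between them is open.

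**Working it through.** **1. Reproduce the plan's figure.** Inputs from Sample size calculation: difference 85.1 − 77.8 = 7.3 h, two-sided alpha 0.05, power 0.80.

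n per group = 2 × (1.960 + 0.842)² × SD² / 7.3²

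- SD 15.6 (the larger pilot SD used for both groups): 2 × 7.849 × 243.36 / 53.29 = 71.7, so **72**. Dropout: 72 / 0.9 = **80**. Both match the plan.
- Pooled SD √((15.6² + 13.35²)/2) = 14.52: **63**, which does not match.

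The plan's 72 therefore rests on SD 15.6, and that basis is used below. The standard error at 72 per group is 15.6 × √(2/72) = 2.60 h. Power is Φ(7.3/2.60 − 1.960) = Φ(0.848) = 0.802.

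**2. Effect of prespecified adjustment.** If the covariates explain a share R² of the outcome variance, the SD becomes 15.6 × √(1 − R²). R² of 0.1 to 0.4 is an assumption.

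| R² | Reduction in SE, 1 − √(1 − R²) | SE (h) | Power at 72 per group | n per group for 80% power |
|---|---|---|---|---|
| 0 | 0 | 2.60 | 0.80 | 72 |
| 0.1 | 5.1% | 2.47 | 0.84 | 65 |
| 0.2 | 10.6% | 2.33 | 0.88 | 58 |
| 0.3 | 16.3% | 2.18 | 0.92 | 51 |
| 0.4 | 22.5% | 2.01 | 0.95 | 44 |

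**3. Chance of a spurious imbalance.** With k independent baseline variables tested at 0.05, the chance of at least one significant result is 1 − 0.95^k: 14% for k = 3, 23% for k = 5, 40% for k = 10. The article gives no number of variables, so k is assumed.

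**4. What a test-triggered rule delivers.** Simulation with 72 per group, SD 15.6, a 7.3 h difference, one normally distributed covariate and 40,000 replicates per scenario:

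| R² | Power, always unadjusted | Power, adjust only if baseline p < 0.05 | Power, always adjusted |
|---|---|---|---|
| 0.1 | 0.798 | 0.801 | 0.834 |
| 0.2 | 0.796 | 0.805 | 0.875 |
| 0.3 | 0.795 | 0.807 | 0.913 |
| 0.4 | 0.799 | 0.816 | 0.950 |

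The triggered rule adjusts in about 5% of trials and captures roughly a tenth of the gain; at R² 0.4, (0.816 − 0.799)/(0.950 − 0.799) ≈ 0.11. Its type I error runs from 0.048 (R² 0.1) down to 0.040 (R² 0.4), so it is slightly conservative. If both analyses were run and the more favourable one reported, type I error would be 0.066 to 0.081.

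**5. Inflammatory markers.** With equal variances and pre–post correlation ρ, the variance of a change-score comparison relative to covariance analysis on baseline is 2(1 − ρ)/(1 − ρ²) = 2/(1 + ρ). For ρ of 0.6 to 0.2 (assumption) this is 1.25 to 1.67.

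**The case against.** **The trigger is not literally stated.** A reader might infer that the protocol makes a significant baseline test the condition for adjustment. The text says only that covariance analysis follows if adjustment is needed, and it is the shared sentence that suggests the link. This stands, and the point is worded accordingly. It does not remove the problem: on any other reading, need is judged by an undefined criterion after the data are seen.

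**Covariate lists belong in an analysis plan.** An article may leave the list to that document, and its absence alone would be no finding. Here, however, the article states a conditional rule, and an analysis plan that followed it would inherit the fault.

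**The unadjusted test is valid and matches the sample size.** This stands. A reader might infer bias or an inflated false-positive rate, and the documents support neither. The triggered rule is slightly conservative, and planned power does not depend on adjustment. The 0.066 to 0.081 range applies only if the better of two results is selected, which the article does not plan, although it does not rank them either.

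**Baseline marker values are used.** A reader might infer that they are ignored. They are not: baseline is one of the three time points and enters the change and repeated-measures analyses. What is missing is its use as a fixed covariate.

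**The population is not unrestricted.** Entry is limited to elective laparoscopic surgery, prior gastric or intestinal surgery and preoperative chemotherapy or radiotherapy are excluded, and mobilisation is the same in both groups. This limits heterogeneity, but organ and malignancy still vary. The documents do not measure how strongly either predicts outcome, so the gain can be given only as a range.

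**Conclusion.** The concern holds as a matter of precision and analytic freedom. Making adjustment depend on baseline comparisons is a poor rule in a randomised trial, and the plan leaves two unranked results. On the protocol's own basis, prespecified adjustment would raise power from about 80% to 84–95%, while a test-triggered rule stays at 80–82%. These figures assume that the covariates explain 10–40% of the variance, and the simulated ones also assume a single covariate.

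Starting from the pooled SD would put unadjusted power at 85%, but that is not the basis on which 72 per group was obtained. The 40% chance of a spurious imbalance applies only if ten independent variables are tested; with three to five it is 14–23%. The change should be made, but the trial is not invalid without it.

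**What to change.** - Delete the baseline homogeneity tests and keep the descriptive baseline table.
- Before unblinding, state that the primary comparison of time to first defecation is the one adjusted for organ group (hepatobiliary, pancreatic, gastric) and malignant versus benign disease, whatever imbalance is observed. Report the unadjusted comparison as supportive.
- Analyse each inflammatory marker with its own baseline value as a fixed covariate, in place of the change-score comparison.

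**Cost.** Organ group and malignancy use three degrees of freedom (two plus one). No new data should be needed: Table 1 lists only general information and medical history, but diagnosis and planned operation must be known to apply the inclusion criteria, and baseline markers are already scheduled. Randomisation and sample size do not change. Because recruitment is under way, the change needs a documented amendment to the analysis plan; made after unblinding, it would look post hoc.

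### The five inflammatory markers have a pre-treatment baseline, but the plan tests their changes and adjusts for baseline only conditionally, which can cost precision on these secondary outcomes

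*Protocol article*

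**What the plan says.** The Inflammatory index section lists five blood markers, "which will be obtained at baseline, 1 day after surgery, and at the time of discharge". Table 1 places the first sample at Visit 2. The Interventions section starts treatment three days before surgery, which is Visit 3 in Table 1, so the baseline value precedes treatment. In Table 1 these markers are the only outcomes with a pre-treatment value.

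The Statistical analysis section has four provisions that bear on them:

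- **Between-group test:** "In terms of the changes in the measurement data, the two-sample *t*-test or the Wilcoxon rank-sum test will be used to compare the two groups", with normality deciding between the two.
- **Repeated measures:** "The mean change and the interaction between groups and observed time frames will be analyzed using a two-factor repeated measure analysis".
- **Mixed model:** allowed where it proves necessary. How baseline would enter it is not stated.
- **Covariance analysis:** allowed where a baseline characteristic calls for adjustment. This clause is attached to the sentence on testing the groups for baseline homogeneity.

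No provision fixes a marker's own baseline value as a covariate.

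**The concern.** Subtracting baseline fixes its slope at 1. If the true regression of the later value on baseline has another slope, subtraction leaves avoidable noise in the comparison. After an operation that itself moves these markers, there is no reason to expect a slope of exactly 1. A covariate model estimates the slope from the data.

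A chance baseline difference between the groups is also carried into the change score through regression to the mean. Averaged over randomisations this is not a bias, but it affects the one trial that is run.

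At stake is the width of the confidence intervals for the markers. The Background section gives anti-inflammatory action as a possible mechanism, and these markers are the only direct measure of inflammation among the listed outcomes. A real difference could be missed although the data to show it had been collected.

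**Working it through.** **The plan's own figure.** For time to first defecation the inputs are "The time to first defecation is 77.8 ± 15.6 h in the intervention group and 85.1 ± 13.35 h in the control group", with two-sided 0.05 and "a power of 0.80, and an allocation ratio of 1:1". The difference is 85.1 − 77.8 = 7.3 h. From n = 2(1.960 + 0.842)² SD² / 7.3²:

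- SD 15.6 (the larger SD) gives 71.7, so 72, the stated number;
- the pooled SD √((15.6² + 13.35²)/2) = 14.52 gives 62.1, so 63.

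Then 72/0.90 = 80, as stated. This calculation does not concern the markers; 72 per group is used below only as a realistic size.

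**Inputs for the markers.** The documents give no SD, correlation or effect for any marker. Assumed: baseline to follow-up correlation ρ from 0.1 to 0.7, and follow-up SD equal to k times baseline SD, with k from 1 to 3.

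**Variances**, with follow-up SD set to 1 and baseline SD to 1/k:

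- change score: 1 + 1/k² − 2ρ/k
- baseline-adjusted: 1 − ρ²
- unadjusted follow-up value: 1

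Change minus adjusted is (ρ − 1/k)², and unadjusted follow-up minus adjusted is ρ². Neither can be negative, so in large samples adjustment is never less precise than either. Against the change score the gain vanishes when ρ = 1/k.

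**Example.** With k = 1 and ρ = 0.5, the change variance is 1 + 1 − 1 = 1.00 and the adjusted variance is 1 − 0.25 = 0.75, which is 25% lower. With k = 2 and ρ = 0.5, both are 0.75 and nothing is gained.

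**Power.** The t-test on change has 80% power at 72 per group for a standardised effect of 0.470 (noncentral t, two-sided 0.05). Multiplying that effect by √(change variance / adjusted variance) gives the adjusted power:

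| k | ρ 0.1 | ρ 0.2 | ρ 0.3 | ρ 0.5 | ρ 0.7 |
|---|---|---|---|---|---|
| 1 | 96.5% | 95.1% | 93.5% | 89.9% | 86.0% |
| 1.5 | 89.7% | 87.4% | 85.1% | 81.4% | 80.1% |
| 2 | 85.5% | 83.4% | 81.7% | 80.0% | 82.9% |
| 3 | 82.1% | 80.7% | 80.0% | 81.4% | 88.3% |

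The gain runs from 0 to 16.5 points.

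**Do the other provisions recover it?**

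- *Repeated measures.* With baseline as a time level, the group-by-time interaction is built from contrasts of change. For baseline and one later time it is the same contrast as the t-test on change. With the three planned times it is a joint test on two degrees of freedom, still of changes.
- *Conditional covariance analysis.* If the trigger is a homogeneity test at 0.05 (an assumption; the plan states only its general level), randomisation alone would trigger it for a given marker in about 5% of trials. The gain comes from the relation of baseline to follow-up, which a test of imbalance does not measure.
- *Mixed model.* It could recover the gain, but it is optional and its handling of baseline is open.

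**The case against.** - **The stated analysis is valid.** Under randomisation these tests control type I error, and the mean difference in change is unbiased. This stands: the point is about efficiency. A reader might infer that the marker results would be biased; the documents do not support that.
- **The plan does provide for adjustment.** A reader might infer that baseline is never adjusted for. That is too strong, because a baseline CRP or IL-6 value is a baseline characteristic and the covariance clause could cover it. What remains is that the adjustment is conditional and tied to the wrong trigger.
- **The word for changes may not mean subtraction of baseline.** The same sentence has to serve the times to defecation and flatus and the hospital stay, which have no baseline. This is fair. If the markers were compared on raw follow-up values with 80% power, scaling the effect by 1/√(1 − ρ²) gives adjusted power of 80.4%, 81.6% and 83.6% at ρ = 0.1, 0.2 and 0.3. The gain is smaller at these correlations but still not negative.
- **The size is assumed.** This stands. With weak correlation (0.1 to 0.3) and a follow-up SD 2 to 3 times baseline, the gain is only 0 to 5.5 points. The documents do not show which case applies.
- **Covariates for secondary markers belong in an analysis plan that is not shown.** Only in part: the article does not leave the method open. It names tests that take no covariate and makes adjustment conditional.

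**Conclusion.** The point holds as one of precision on secondary outcomes. A pre-treatment value exists for all five markers, the named tests do not use it as a covariate, and none of the other provisions is certain to do so.

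On the assumed grid, baseline adjustment turns 80% power for the t-test on change into anything from 80.0% to 96.5%. The figures rest on assumed correlations and SD ratios, on 72 per group with complete data, and on the t-test; the rank-sum test on changes was not calculated. No single figure for the loss can be defended from the documents, and it may be close to nil for some markers.

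A reader might also infer that the trial's main comparison is underpowered for this reason. It is not: time to first defecation and time to first flatus have no baseline value, so the point does not touch them. The case for the change is that the large-sample gain is never negative and the cost is very small.

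**What to change.** In the Statistical analysis section, state for each of WBC, CRP, IL-6, PCT and TNF-α that the main between-group comparison at day 1 and at discharge is one of these:

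- analysis of covariance of the post-operative value on group, with that marker's baseline value as covariate, using the log scale for both if the marker is skewed; or
- the mixed model already allowed, with the post-operative values as responses, baseline and baseline-by-time as covariates, and the group contrast reported at each time with its 95% confidence interval.

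State that this applies to all patients whatever the homogeneity tests show. The t-test or rank-sum test on changes can stay as a supporting analysis.

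The cost is wording, best settled before anyone analyses the data by group. It needs no new samples, visits or patients, and the stated software fits these models. The downsides are small: one degree of freedom for each analysis of covariance and, on the log scale, results given as ratios of geometric means in place of raw changes.
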